**Fig. 1 Fig1:**
[figure not shown]
Trial flow

**Fig. 2 Fig2:**
[figure not shown]
Trial process

### Blinding

No blinding method will be used in this experiment. Blinding is not feasible for this study for patients or the research team. The data analyst is also involved directly with the study processes and data collection, and thus blinding of the analyst is not possible.

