### Randomization

Treatment allocation occurs when the study participant meets the inclusion criteria and signs the informed consent form. All eligible patients will receive ATRA-ATO for induction therapy. Participants are randomized by permuted blocks to ensure there are similar numbers of participants in the intervention and control groups. The randomization allocation schedule is generated by a statistician with no other involvement in the study. Once consented, participants are allocated in a 1:1 ratio to the two arms of the study according to a computer-generated random sequence after achieving hematologic complete remission (HCR) (Figs. 1 and 2). Participants will be informed of their allocated treatment group following randomization.

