### Outcome measures

In this trial, we selected 2-year DFS rates as the primary outcome. Any of the following events will be considered a failure: no achievement of HCR after induction therapy, relapse, or death. HCR is defined as follows [12]: hematologic complete remission: bone marrow blasts < 5%; absence of circulating blasts and blasts with Auer rods; absence of extramedullary disease; absolute neutrophil count > 1.0 × 10^9^/L; platelet count > 100 × 10^9^/L.

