### Data collection and management

Patient information will be entered into the paper case report forms (CRFs) promptly and synchronously with input into the electronic CRF. The occurrence of unexpected problems during this process should be recorded, and will be informed in a timely manner.

In order to ascertain the two randomized groups are similar, the demographic/disease characteristics including sex, age, region, body mass index (BMI) and medical history will be collected.

The committee that was responsible for the study design and the implementation process will ensure the effectiveness and integrity of the trial design. The committee will supervise the integrity and accuracy of data collection to control its quality. The committee also needs to evaluate key outcomes based on the clinical expertise of its members.

Data sharing is not applicable to this protocol article as no datasets have as yet been generated or analyzed during the current study. The results should be made public within 24 months of reaching the end of the study. The end of the study is the time point at which the last data items are to be reported, or after the outcomes of data are sufficiently mature for analysis as defined in the statistical analysis section. A full report of the outcomes should be made public no later than 3 years after the end of the study. Results will also be available through the Clinical Trials Registry.

Missing data will be reviewed to identify potential patterns, and examined to assess how these patterns impact our results. There are three types of missing data that can occur when the data are being collected [13]. When data are missing (completely) at random, unbiased results can still be obtained using the maximum likelihood method that will be used in the linear mixed model analysis. When data are not missing at random, we will analyze sensitivity using pattern mixture models and the results will be used to assess the impact of missing data on the reported conclusions.

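### Relapse is judged and the data are analysed with no masking, although one relapse call can decide non-inferiority and reading relapse without knowledge of the arm looks feasible

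*Protocol article*

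**What the plan says.** All places are in the Methods of the protocol article.

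- **Blinding** opens with a general rule, "No blinding method will be used in this experiment", and adds: "Blinding is not feasible for this study for patients or the research team". A separate reason follows for the analysis: "The data analyst is also involved directly with the study processes and data collection, and thus blinding of the analyst is not possible".
- **Data collection and management** describes a committee: "The committee that was responsible for the study design and the implementation process will ensure the effectiveness and integrity of the trial design". The same paragraph continues: "The committee also needs to evaluate key outcomes based on the clinical expertise of its members". It does not say whether the committee sees the arm.
- **Randomization** places allocation after hematologic complete remission and names one person outside the trial team: "The randomization allocation schedule is generated by a statistician with no other involvement in the study".
- **Outcome measures**: "we selected 2-year DFS rates as the primary outcome", with these failures: "no achievement of HCR after induction therapy, relapse, or death". Relapse is hematologic (marrow blasts with a 5% threshold, blasts in blood, extramedullary disease) or molecular (return of minimal residual disease by RT-qPCR or flow cytometry).
- **Follow-up monitoring** sets PCR every 3 months for 2 years. A positive result is repeated within 4 weeks.

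**The concern.** Two different reasons are run together. That patients and treating clinicians cannot be masked is plain when one drug is swallowed at home and the other infused in hospital. It does not follow that the people who classify a relapse, or who run the primary comparison, must know the arm. For the analyst, the only obstacle named is that the same person also collects data, and the team chose that arrangement. For outcome evaluation no separate reason is given: it falls under the general no-blinding rule.

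The setting makes this matter. The Study hypothesis section expects RIF with ATRA to be non-inferior and to improve efficacy. In a non-inferiority comparison with very few failures, not counting a doubtful RIF relapse moves the result toward that expectation. If one such call can change the conclusion, readers will ask who made it and what that person knew.

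**Working it through.** **Inputs** (Sample size calculation): 2-year DFS 97% for ATO and 99% for RIF; margin −5 points; one-sided 5% error; 90% power; 53 evaluable and 59 enrolled per arm.

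**Assumption.** The Statistical analysis section names no non-inferiority test, so I use the difference in 2-year DFS proportions.

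**The plan's own figure.** Exact binomial enumeration of a z-test for this difference gives power 85.7% at 52 per arm and 91.9% at 53. The stated 53 is therefore reproduced as the first n, scanning from 40, to reach 90%. Then 53/0.90 = 58.9, so 59 per arm and 118 in total. Masking changes none of these.

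**Step 1: which failures are open to judgement.**
- No remission after induction: reached or missed before randomisation, so it cannot be called differently by arm.
- Death: objective.
- Relapse: open in part. Marrow counts near the threshold and flow or qPCR readings need interpretation. The relapse definition does not require confirmation, while the follow-up section repeats a positive PCR. A positive result that is not confirmed is therefore a doubtful case that someone must settle.

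**Step 2: weight of one event.** Expected failures are 59 × 0.03 + 59 × 0.01 = 1.77 + 0.59 = 2.36. One event shifts an arm's DFS by 1/59 = 1.7 points, and 1.7/5 is about a third of the margin.

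**Step 3: can one call change the conclusion?** Let d = p(RIF) − p(ATO), with 59 per arm and 2 ATO failures, so p(ATO) = 57/59 = 0.9661.

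- Wald lower limit: d − 1.645 × √[p(RIF)(1 − p(RIF))/59 + p(ATO)(1 − p(ATO))/59].
  - 1 RIF failure: 0.0169 − 1.645 × 0.0289 = −0.031.
  - 2 RIF failures: 0 − 1.645 × 0.0333 = −0.055.
- Farrington-Manning score: z = (d + 0.05)/SE, with SE from the rates fitted under a true difference of −5 points.
  - 1 RIF failure: 0.0669/0.0374 = 1.79.
  - 2 RIF failures: 0.05/0.0386 = 1.30. The cut is 1.645.
- Newcombe lower limit: d − √[(p(RIF) − L)² + (U − p(ATO))²], with L and U the 90% Wilson limits.
  - 1 RIF failure: 0.0169 − √(0.0555² + 0.0226²) = −0.043.
  - 2 RIF failures: 0 − √(0.0635² + 0.0226²) = −0.067.

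| Per arm | ATO failures | RIF failures | Score z | Wald limit (points) | Newcombe limit (points) | Non-inferior? |
|---|---|---|---|---|---|---|
| 59 | 2 | 1 | 1.79 | −3.1 | −4.3 | yes, all three |
| 59 | 2 | 2 | 1.30 | −5.5 | −6.7 | no, all three |
| 53 | 2 | 1 | 1.70 | −3.4 | −4.7 | yes, all three |
| 53 | 2 | 2 | 1.19 | −6.1 | −7.4 | no, all three |

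With 0 or 1 ATO failure, the Wald method still loses non-inferiority at the second RIF failure; the score and Newcombe methods lose it at the first.

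**Step 4: how often the result sits this close.** With the z-test at 59 per arm, the chance of lying one RIF event from the boundary is 34% at 97%/99% and 53% if both arms are at 97% (33% and 54% at 53 per arm). At 59 per arm, the part in which one missed RIF failure would turn a failed trial into a successful one is 7.6% and 23.9% respectively. The rest are passes that one further RIF event would undo.

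**The case against.** The strongest reply has four parts.

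1. **The endpoint is fairly hard.** Death and pre-randomisation remission leave no room, PCR follows a fixed schedule, and the repeat test limits discretion. This stands. It narrows the concern to relapse readings and doubtful cases, and does not remove it.
2. **The flip measures fragility.** A small trial with few events would turn on one event even under perfect masking, and nothing in the document shows how often an open-label reader would miscall. The pair in the table is also one of many: at planning rates and 59 per arm, exactly 2 ATO and 1 RIF failures has probability of about 9%, and 2 and 2 about 3%. This stands too.
3. **The article discloses an open-label design, and the committee's working rules may be in the full protocol.** Partly right. The article does not say that the committee classifies every relapse. But the no-blinding rule and the claim that the analyst cannot be masked are stated here, and the reason given for the second does not support it.
4. **Masking the analyst adds little.** Hospital days and costs would reveal the arms once seen. That is fair, and it is why dummy codes rank below masked relapse review.

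A reader might also infer that masking is free because samples are already coded and an independent statistician already holds the allocation list. The document says neither. It names the tests without describing sample labels, and it says that the statistician generates the schedule, not that this person keeps it. Nor does the sentence about the analyst explain unmasked outcome evaluation; that follows from the two sentences before it and from the committee's role.

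**Conclusion.** The point holds in limited form. Open-label treatment is justified. Extending no blinding to relapse classification and to the primary analysis is not justified by the reasons given, and the analyst's double role is a choice. The exposed judgement is relapse.

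Assuming a comparison of 2-year proportions against the 5-point margin, one RIF relapse call separates success from failure at 2 ATO failures, whether 53 or 59 per arm are counted and by all three methods. At the planning rates, the z-test result lies one RIF event from the boundary about a third of the time.

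The stronger reading, that the result is or will be biased, is not supported: no miscall rate is given or can be derived. The change is worth making because it removes an avoidable doubt about a conclusion that can rest on one patient.

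**What to change.** Amend the Blinding section and the committee paragraph in Data collection and management so that:

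- (a) marrow, PCR and flow cytometry samples go to the laboratory under study number only;
- (b) the existing committee classifies each possible relapse, including a positive PCR not confirmed on repeat, from case files with arm and drug details removed, before the event list is locked;
- (c) as a lesser safeguard, the primary analysis is programmed on dummy arm codes until that lock, with the key kept by someone outside data collection. The statistician who generated the schedule could do this, if that person agrees to the added role.

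The statement that the analyst cannot be masked should be replaced by a description of what is and is not masked.

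Sample size, treatment and visits do not change. The cost is relabelling of samples, redaction of a handful of event files, and a key-holding arrangement. Masking will be imperfect: there are two hospitals, recruitment began in July 2016, and committee members or the analyst may recognise patients or already know some allocations.

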### Interventions

Patients with APL will be randomly assigned by a computer-generated, random-allocation schedule to one of two groups: the ATRA-RIF group (experimental group); the ATRA-ATO group (control group); patients with APL will be classified into three risk categories on the basis of WBC count and platelet count. Low risk is a WBC count < 10 × 10^9^/L and a platelet count ≥40 × 10^9^/L; intermediate risk is a WBC count < 10 × 10^9^/L and a platelet count < 40 × 10^9^/L; high risk is a WBC count ≥ 10 × 10^9^/L (Fig. 3).

**Fig. 3 Fig3:**

Treatment groups. ATO, arsenic trioxide; ATRA, all-trans retinoic acid; APL, acute promyelocytic leukemia; HCR, hematologic complete remission; MCR, molecular complete remission; RIF, realgar-indigo naturalis formula

### Induction therapy

The induction therapy is ATRA 60 mg/day (20–45 mg/m^2^ body surface area/day) plus ATO (0.15 mg/kg body weight/day), which will be maintained until HCR. Hydroxyurea will be used in patients who develop leukocytosis during induction therapy. Four blood tests are performed per week during induction therapy. The blood routine should be tested everyday in the first week of induction therapy.

### Consolidation therapy

#### ATRA-RIF group

The ATRA-RIF group will receive ATRA 60 mg/day (20–45 mg/m^2^/day) plus oral RIF (60 mg/kg/day) 2 weeks on and 2 to ~ 4 weeks off, until PML-retinoic acid receptor alpha (RARα) is negative by reverse transcriptase-polymerase chain reaction (RT-PCR), then ATRA and oral RIF 2 weeks on and 2 to ~ 4 weeks off, giving a total of six courses.

#### ATRA-ATO group

ATRA 60 mg/day (20–45 mg/m^2^/day) plus ATO (0.15 mg/kg/day) 2 weeks on and 2 to ~ 4 weeks off, until PML-RARα is negative by RT-PCR, then ATRA and ATO 2 weeks on and 2 to ~ 4 weeks off, giving a total of six courses.

The PML-RARα fusion gene will be detected by RT-PCR before every cycle of consolidation therapy. The liver and kidney function, blood coagulation, electrocardiogram, arsenic concentration in blood and urine will be checked at least once a week during the whole treatment.

Regarding management of differentiation syndrome (DS) for the two groups: the hydroxyurea should be given at the earliest manifestations of suspected DS and hyperleukocytosis. At the same time, intravenously administered dexamethasone is administered at a dose of 10 mg every 12 h until the disappearance of signs and symptoms for a minimum of 3 days. The ATRA can still be given, but the dose of ATRA should be reduced by as much as half the conventional dose.

### Monitoring

#### Follow-up monitoring

We will monitor bone marrow samples by PCR every 3 months after finishing the consolidation therapy to detect molecular relapse. The sustained observation will last for 2 years. If the PML-RARα gene expression is positive, PCR will be repeated for confirmation within 4 weeks. If the PML-RARα gene expression is negative, the patients need to proceed to consolidation therapy or conversely the patient needs to be treated for relapse.

#### Data monitoring

The study progress, safety data and data quality will be monitored by The Clinical Research Center of the First Affiliated Hospital of Xi’an Jiaotong University.

### Harms

Every case of hyperleukocytosis and QT-interval prolongation occurring during the study must be recorded. The following information will be recorded: occurrence time, severity, duration, adopted measure, and the outcome of the adverse event.

### Baseline characteristics

Baseline characteristics in each group will be analyzed using descriptive statistics, including means or medians for continuous variables and percentages for categorical variables.

### Outcome measures

In this trial, we selected 2-year DFS rates as the primary outcome. Any of the following events will be considered a failure: no achievement of HCR after induction therapy, relapse, or death. HCR is defined as follows [12]: hematologic complete remission: bone marrow blasts < 5%; absence of circulating blasts and blasts with Auer rods; absence of extramedullary disease; absolute neutrophil count > 1.0 × 10^9^/L; platelet count > 100 × 10^9^/L.

#### Relapse is defined as follow [12]:

Hematologic relapse is defined by bone marrow blasts of 5%, reappearance of blasts in the blood, or development of extramedullary disease. Molecular relapse: if studied pre-treatment it is defined by recurrence of minimal residual disease (MRD) as assessed by quantitative RT-qPCR or by multi-color flow cytometry.

The secondary outcomes of this trial are hospitalization days and medical costs in the two arms. The medical costs will be calculated for each patient. The hospitalization costs for induction and consolidation therapy will be calculated for inpatients. The hospital costs for induction therapy and consolidation therapy will be calculated for outpatients. All medical costs can be collected and multiplied by the unit cost of each resource use. After the patient is discharged from the hospital, we can obtain the medical costs from the medical record in hospital according to the patient’s name/case number. For the outpatients, the medical costs can be obtained from the outpatient system after the patient’s visit. Hospitalization days will be recorded over a 10-month time frame.

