**Methods:**

This study was designed as a multicenter, randomized controlled trial. The trial has a non-inferiority design with superiority being explored if non-inferiority is identified. All patients receive ATRA-ATO during the induction therapy. After achieving hematologic complete remission (HCR), patients were randomly assigned (1:1) to receive treatment with ATRA-RIF (experimental group) or ATRA-ATO (control group) as the consolidation therapy. During the consolidation therapy, the two groups receive ATRA plus RIF or intravenous ATO 2 weeks on and 2 to ~ 4 weeks off until molecular complete remission (MCR), then ATRA and oral RIF 2 weeks on and 2 to ~ 4 weeks off giving a total of six courses.

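### The between-arm medical-cost outcome counts induction costs, which are settled before randomisation and add noise that the randomised drug cannot affect

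*Protocol article*

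**What the plan says.** The end of the Outcome measures section, under the sub-heading that defines relapse, sets the secondary outcomes: "The secondary outcomes of this trial are hospitalization days and medical costs in the two arms". On costs it adds "The hospitalization costs for induction and consolidation therapy will be calculated for inpatients" and "The hospital costs for induction therapy and consolidation therapy will be calculated for outpatients". On hospital stay it says only "Hospitalization days will be recorded over a 10-month time frame"; it gives no start point and does not mention induction.

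The Randomization section says "All eligible patients will receive ATRA-ATO for induction therapy", and that patients are allocated "according to a computer-generated random sequence after achieving hematologic complete remission (HCR". The Abstract agrees: "After achieving hematologic complete remission (HCR), patients were randomly assigned (1:1". Another sentence in the Randomization section instead ties allocation to eligibility and consent.

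The Discussion locates the difference in care setting in remission therapy: RIF at home, ATO in hospital. The Abstract and the Study hypothesis state the aim as lowering total hospital days and medical costs.

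**The concern.** A between-arm outcome should measure what the assigned treatment can change. Here the first part of each patient's cost has been incurred before assignment, under a regimen planned to be the same for everyone. That part carries no treatment effect, only variation between patients.

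Precision and interpretation are both at stake. The added variance widens the interval, and a chance difference between arms in induction cost passes straight into the estimated saving. A percentage saving on the total is also smaller than the percentage saving in the phase where the arms differ.

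Fixing the period in advance matters more than usual in this trial. The Statistical analysis section describes the cost comparison as retrospective and post hoc, and the Blinding section says the analyst is not blinded.

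**Working it through.** **Plan's own figures.** The article gives no expected difference, SD or power for costs or days. Its only sample size is for 2-year DFS: 53 evaluable per group, 53/0.9 = 58.9, so 59 per group and 118 in total. I use 59 per arm below only as the number available for the cost comparison.

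**Is induction cost fixed before assignment?** Induction is ATRA-ATO for all and continues until remission; randomisation follows remission; the cost sentences name induction. Taken together, yes for costs.

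**Bias.** Write the total as T = I + C, with I the induction cost and C the consolidation cost. With randomisation after remission, I has the same expectation in both arms, so

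E(T in ATO) − E(T in RIF) = E(C in ATO) − E(C in RIF).

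The absolute difference in mean total is unbiased for the consolidation effect.

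**Precision.** Let r = SD(I)/SD(C) and ρ = their correlation. Then Var(T)/Var(C) = 1 + r² + 2ρr, and the standard error of the arm difference grows by the square root of this. The documents give neither r nor ρ, so the table is a range under assumptions. The power columns take an effect that consolidation cost alone would detect with 90% power at 59 per arm (two-sided 0.05), using power ≈ Φ(3.2415/√(variance factor) − 1.960), where 3.2415 = 1.960 + 1.2815.

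| r | Variance factor, ρ = 0 | SE factor, ρ = 0 | Power, ρ = 0 | Variance factor, ρ = 0.3 | Power, ρ = 0.3 |
|---|---|---|---|---|---|
| 0.5 | 1.25 | 1.118 (+12%) | 0.826 | 1.55 | 0.740 |
| 1 | 2.00 | 1.414 (+41%) | 0.630 | 2.60 | 0.520 |
| 2 | 5.00 | 2.236 (+124%) | 0.305 | 6.20 | 0.255 |

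The total would be less variable than consolidation cost alone only if ρ were below −r/2.

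**Chance imbalance.** The arm difference in mean induction cost has expectation zero and standard error √(2/59) = 0.18 induction SDs (√(2/53) = 0.19 with 53 per arm).

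**Dilution.** The relative saving on the total is (C_ATO − C_RIF)/(C_ATO + I), which falls as I grows. No costs are given, so I illustrate in days, assuming 30 induction days, 6 × 14 = 84 inpatient days on ATO and none on RIF. Totals are 114 and 30. The absolute saving is 84 days with or without induction. The relative saving is 84/114 = 74% on the total, against 84/84 = 100% after randomisation.

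**Do hospital days include induction?** Six courses of 4 to 6 weeks take 24 to 36 weeks. Adding about 30 days to remission (Discussion) gives about 28 to 40 weeks. Ten months is about 43 weeks, so the window holds the schedule either way. The Discussion also describes six courses after the fusion gene is negative, with 2 to 6 months to molecular remission. Counted from the start of treatment, that gives 5.5 + 2 = 7.5 to 8.3 + 6 = 14.3 months. The length of the window therefore cannot show where it starts.

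**Effect of adjustment.** Since T = I + C, a linear regression of T on arm and I gives the same arm coefficient and standard error as a regression of C on arm and I; only the coefficient of I changes, by 1. Adjusting the total therefore removes the added noise, with residual variance (1 − ρ²)Var(C).

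**The case against.** The best defence is that a whole-treatment total is a legitimate quantity for patients and payers, and that it matches the stated aim. The cost sentences say what will be calculated. They do not say that the phases will only be summed, and they are compatible with reporting by phase. This stands, and it is why the total should be kept as a description. What remains is that the text names induction in a between-arm outcome and does not commit to a comparison from randomisation.

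The defence can also say that the loss may not matter. In the illustration above, an assumed induction SD of 10 to 20 days gives a chance difference with standard error 0.184 × 10 = 1.8 to 0.184 × 20 = 3.7 days, against a saving of 84. If the cost saving is comparably large, the extra noise will not change the conclusion. This also stands; the documents do not give the figures to decide it. The named test for costs is rank-based, which limits the pull of a few extreme inductions on the test, though not the extra spread. (That its matched-pairs form does not suit independent arms is a separate matter.)

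Some stronger readings are tempting but are not supported:

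- That the cost comparison is biased, or that the total fails to estimate the consolidation effect. Randomisation after remission balances induction cost in expectation, and the absolute difference is unaffected.
- That hospital days are known to include induction. The article does not say so, and the 10-month window fits both readings.
- That induction costs are counted twice. The two sentences list inpatient and outpatient settings.
- That induction is identical in realised cost. Only the planned regimen is the same.

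The sentence tying allocation to consent conflicts with allocation after remission and needs reconciling. On either reading, the planned induction regimen is common to both arms.

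**Conclusion.** The point holds for medical costs. The article counts induction cost in a between-arm outcome although that cost is settled before randomisation after remission. The consequences are lost precision, chance imbalance and a diluted relative saving; there is no systematic bias in the absolute difference in means.

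The 12%, 41% and 124% increases in standard error are correct arithmetic for assumed SD ratios of 0.5, 1 and 2 under independence. They are not estimates for this trial. For hospital days, the finding is only that the start of the window is undefined.

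Priority is minor: secondary outcomes only, with no bearing on the DFS comparison or its sample size.

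**What to change.** - Make the main between-arm cost comparison run from randomisation to the end of consolidation, or compare whole-treatment cost with induction cost as a baseline covariate. State which before the analysis.
- Start the hospital-day window at randomisation, so that days and costs cover the same period.
- Report induction costs and days separately by arm, and keep the whole-treatment total beside them as a description, since it answers the stated aim.
- Reconcile the two statements on when allocation occurs, and the two descriptions of the six courses, because they set the start and the end of this period.

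The change is one of wording. Costs come from hospital and outpatient records; provided these can be split at the randomisation date, no new data are needed. The downside is that the whole-treatment total is no longer the main comparison.
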